### Pretreatment evaluation

All patients who are potential candidates for hepatopancreatobiliary surgery will undergo a standard evaluation that will include contrast-enhanced computed tomography (CT), endoluminal ultrasound (EUS), magnetic resonance imaging (MRI), and positron emission tomography (PET-CT), which will be discussed at the preoperative conference.

Patients recommended for major hepatopancreatobiliary surgery (such as a liver resection, pancreaticoduodenectomy, or total/distal pancreatectomy) will be contacted and provided with a participant information sheet. Patients will be divided into three groups according to the type of surgery.

### Treatment

#### Trial intervention

Patients receiving dietary supplementation with mealworms after their pancreatectomy, bile duct resection and hepatectomy will be given the mealworms during their hospitalization period and for another 2 months after discharge. The patients in group A will undergo enteral feeding after surgery (for those who undergo a pancreaticoduodenectomy, nutrients will be administered by an enteral feeding tube for early feeding while securing the pancreatojejunostomy). A feeding nasojejunal tube will be placed for patients in the enteral feeding group. Enteral feeding (Newcare 300 RTH, Daesang, Korea) will start within 24 h postoperatively at a rate of 20 mL/h. The velocity will be progressively increased by 20 mL/d until reaching the full nutritional goal (25 kcal/kg). Enteral feeding will be delivered by an infusion pump for 18 h/day with 6 h of rest.

On postoperative day 7, abdominal and pelvic CT scans will be obtained, and if there are no complications, we will then start patients on a clear liquid diet for 1 day. In addition, the patients will be permitted to have a full liquid diet for 2 days and then a soft diet for 3 days following the liquid diet.

The patients of group B will undergo oral feeding 2 days after the surgery. (distal pancreatectomy, total pancreatectomy and bile duct resection) We will start patient’s clear liquid diet for 1 day. The patients will be permitted to have a full liquid diet for 2 days and soft diet for 3 days following the liquid diet.

The patients of group C will undergo oral feeding 2 days after surgery (which includes liver resections). We will then start the patients on a clear liquid diet for 1 day. In addition, the patients will be permitted to have a full liquid diet for 2 days and soft diet for 3 days following the liquid diet. The mealworm powder include 3 g of carbohydrate, 14.4 g of protein and 11 g of fat, 163 kcal per 30 g. (Table 1) As a result of a nutritional analysis of mealworm powder, 10.28 g of carbohydrate, 48.26 g of protein and 35.81 g of fat were found per 100 g. In particular, the protein includes essential amino acids as well as many unsaturated fatty acids ranging from 76 to 80% of the total fatty acids. In addition, iron and calcium and other minerals were found (Table 2).

**Table 1 Tab1:**
[figure not shown]
Components of the Trial group’s diet

**Table 2 Tab2:** Menu plan and protocol of the hospital meals for the mealworm and control groups

			Mealworm group	Control group
Step 1	Menu Nutrient	Energy Protein Carbohydrate Fat	Carbohydrate-based liquid diet, Mealworm jelly 580 kcal 13 g 114 g 8 g	Carbohydrate-based liquid diet, Juice 450 kcal 16 g 84 g 6 g
Step 2	Menu Nutrient	Energy Protein Carbohydrate Fat	Mealworm soup, Mealworm shake with berry, Protein-fortified gelatin 1220 kcal 50 g 180 g 34 g	Carbohydrate-based liquid diet, Thin low-fat soup, Soybean milk, Protein-fortified gelatin 1240 kcal 43 g 180 g 39 g
Step 3	Menu Nutrient	Energy Protein Carbohydrate Fat	Deluxe rice porridge with soft side dishes, ONS1)-based mealworm drink, Mealworm tea-confectionery 1629 kcal 81 g 225 g 45 g	Rice porridge with soft side dishes 1600 kcal 75 g 235 g 40 g
Protocol			The doctor prescribes Step 1 diet (clear liquid diet) as the first meal after surgery. Patients eat this diet for 2–3 meals. As the next meal, the doctor prescribes Step 2 diet (full liquid diet). Patients eat this diet for 2–3 meals. If the diet transition goes smoothly, the doctor prescribes Step 3 diet (soft diet). Patients eat this diet until discharge. The doctor prescribes hospital meal intake. Depending on the patient’s condition, the steps for consuming the diet could be adjusted. The dietitian surveys the dietary intake every day until discharge. If there is a meal-related side effect, it is reported to the doctor.	

#### Control intervention

Patients receiving dietary supplementation with grainpowder after pancreatectomy and hepatectomy will be given grainpowder for their hospitalization period and 2 months after discharge. The grainpowder include 23 g of carbohydrate, 2.9 g of protein and 0.5 g of fat, 106 kcal per 30 g. Group A will receive the grainpowder on postoperative day 7. And group B and C will receive grainpowder in the same dose as trial group’s mealworms at the start of diet at postoperative 2 days (Table 3).

**Table 3 Tab3:**
[figure not shown]
Components of the Control group’s diet

#### Outcome measures

The primary outcome is the body cell mass index as measured by body composition (Inbody S-10 (Biospace, Seoul, Korea)). The secondary outcome measures are as follows: nutritional index (weight, soft lean mass, fat free mass, fat mass, PG-SGA [Scored Patient-Generated Subjective Global Assessment]) and immune function test (that assesses T cells, B cells, cytokines). We will confirm changes in immune cells through FACS (fluorescence-activated cell sorting). Based on the immune assay using blood samples from patients, we will identify changes in several cytokines.

### Timeline and recruitment

#### Recruitment of study participants

Once the patients’ surgery is confirmed, the research staff will give the study staff a list of the patients. After determining the suitability of the patient, the study staff will assign the patient to the test or control group in a randomized sequence in the order in which they are enrolled. In addition, they will be assigned in a double-blinded manner.

#### Randomization

The researchers will select patients after obtaining consent. Randomization will take place via an allocation randomization system 2 days before the surgery, which will be directed by our department. Patients will be randomized to one of the treatment groups in a 1:1 ratio. After consent for study enrollment is obtained, the randomization process will be applied to identify the next allotment. The surgeons will be blind to the allotment throughout the enrollment process.

#### Blinding

Patients and all team members will be blinded to the intervention. Adverse event (AE) and serious adverse event (SAE) need to be reported as soon as they are noted. This will not have any impact on the endpoint assessment of the patient.

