# Clinical application of invalid foods using mealworms and evaluation of nutrition status and immune function: a study protocol for a randomized, double blind, placebo-controlled trial

**DOI:** 10.1186/s40795-019-0307-6

**Published:** 2019-11-18

**Keywords:** Nutritional balance, Malnutrition, Immune function, Invalid foods

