#### Data management

The amount of food consumed by the patient daily will be assessed as a diary entry. The researcher collects the bags left over from the patients at the outpatient clinic. Individual participant medical information obtained as a result of this study is considered confidential and disclosure to third parties is prohibited. Blood samples transferred to the laboratory of Gangnam Severance Hospital will be identifiable by unique trial numbers only. Results related to nutrient indicators (Inbody, PG-SGA) will be managed by a Gangnam Severance Nutrition Team. The blood sample associated with the immune function test will be transferred to the lab of the study staff in Gangnam Severance Hospital, which will then undergo FACS (Fluorescence-activated cell sorting).

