#### Monitoring and follow-up period

The research team is responsible for monitoring the study. At 1 week after discharge, the participants are asked whether they are willing to continue ingesting the mealworm. Every 2 weeks after the patients visit their outpatient clinic, the monitoring researcher will check whether they are taking the mealworm regularly. The research team is also responsible for systematically reviewing the causes of withdrawal from the study. Assessment of these changes will be determined 2 months after surgery (Table 4).

**Table 4 Tab4:** Clinical trial timeline

		Study period				
		Enrolment	Allocation	Postoperative day		
Timepoint		Day − 2	Day − 1	1	7	60
Enrolment						
Initial eligibility screening		◆				
Informed consent		◆				
Allocation			◆			
Interventions	Mealworm diet			◆	◆	◆
	Control diet			◆	◆	
Assessments 1)Anthropometry 2)Nutrition index 3)Blood test 4)Immune function evaluation	Height, weight, BMI Body composition PG-SGA					
			◆			◆
			◆			◆
	Complete blood count Liver function test Renal function test		◆	◆	◆	◆
	Immune function		◆	◆	◆	◆

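### The protocol says patients and all team members are blinded, but its own menus and post-discharge checks contradict this

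*Protocol article*

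**What the plan says.** The claim of blinding appears in several places in the protocol article. The title describes "a study protocol for a randomized, double blind, placebo-controlled trial". Under Recruitment of study participants, "they will be assigned in a double-blinded manner". The Blinding section has no exceptions: "Patients and all team members will be blinded to the intervention". The Randomization section is narrower: "The surgeons will be blind to the allotment throughout the enrollment process".

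The procedures are described elsewhere. Table 2 sets out separate hospital menus by arm. At Step 2, for example, the trial arm receives "Mealworm soup, Mealworm shake with berry, Protein-fortified gelatin". The same table has the doctor prescribing each step and the dietitian surveying intake every day until discharge.

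For the period after discharge, Monitoring and follow-up period says: "At 1 week after discharge, the participants are asked whether they are willing to continue ingesting the mealworm". At the two-weekly outpatient visits, "the monitoring researcher will check whether they are taking the mealworm regularly".

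Under Data management, "Results related to nutrient indicators (Inbody, PG-SGA) will be managed by" the hospital's nutrition team, and blood samples carry trial numbers only.

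**The concern.** Blinding of everyone is a property on which readers will rely when they judge the result. If staff or patients can tell the arm, outcomes that depend on report or behaviour may respond to that knowledge. Here these are PG-SGA, which is patient-generated; intake, which is recorded in a diary; adherence; and withdrawal, for which no reason is needed.

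The primary outcome, body cell mass index by InBody S-10, is a device reading and less open to direct influence. It can still be affected through what patients eat. If adherence were prompted in one arm only, that would be a co-intervention acting on intake, and so on the primary comparison.

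**Working it through.** No figure in the plan bears on this point, so the check sets the passages side by side.

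**1. Hospital menus (Table 2)**

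| Step | Mealworm arm only | Control arm only | Shared |
|---|---|---|---|
| 1 | mealworm jelly | juice | carbohydrate-based liquid diet |
| 2 | mealworm soup, mealworm shake with berry | carbohydrate-based liquid diet, thin low-fat soup, soybean milk | protein-fortified gelatin |
| 3 | mealworm drink, mealworm tea-confectionery | none listed | rice porridge with soft side dishes (called deluxe in the mealworm arm) |

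Items differ by arm at 3 of 3 steps. Step 3, which lasts until discharge, lists a drink and a confectionery for one arm and nothing in their place for the other. This is a difference in the kind of food served, whatever name the patient is shown.

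**2. Who meets these menus**

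- *Dietitian.* A daily survey of intake requires knowing which items were served and eaten. Since the items differ by arm, the dietitian can identify the arm.
- *Doctor.* The prescription is written by step, and the step names are the same in both arms. Whether the doctor sees the arm is not stated.
- *Patient.* Each patient sees one menu, not both. What the items are called at the bedside is not stated. Recognition is plausible, especially at Step 3, but not established.

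**3. Checks after discharge (Monitoring and follow-up period)**

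- If only mealworm patients are asked, the researcher knows the arm and controls have no matching check.
- If all patients are asked as written, controls are asked about a product they were not given. A truthful answer then reveals the arm.
- If mealworm is loose wording for either powder, blinding could survive at this step, but the text does not say so.

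The first two readings, which take the words as they stand, conflict with the Blinding section.

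**4. Number of checks potentially affected**

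This is only a rough range, because the date of discharge is not given.

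- From surgery to day 60: 60 / 14 = 4.3, about 4 checks.
- For Group A, assuming discharge when the diet steps end: 7 + 1 + 2 + 3 = day 13; (60 − 13) / 14 = 3.4, about 3 checks.
- If the window is instead 2 months after discharge, as both intervention sections state, taken as 60 days: 60 / 14 = 4.3, again about 4.

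**5. Comparator powder**

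Per 30 g, the mealworm powder has 14.4 g protein and 11 g fat, and the grain powder 2.9 g and 0.5 g (Trial intervention; Control intervention). Equal dose is stated for Groups B and C. Matching of appearance, taste or packaging is not described.

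**6. What blinding remains**

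Surgeons are blind during enrolment (Randomization), and blood samples are coded (Data management). Neither covers ward staff, the monitoring researcher or patients.

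**The case against.** The strongest reply is that an article condenses the full protocol, which may describe masking of the powder and the meals. Table 2 is a menu plan for staff, not a label shown to patients. The arms share several items, and powder mixed into a soup or shake may not be recognisable. The take-home phase, which is the longer exposure, uses a powder in both arms. The monitoring text speaks of participants generally, and the diary and the collection of leftover bags are described for all patients, so loose wording is at least as likely as checks in one arm only. The primary outcome is a device reading, and managing results is not the same as taking the measurement.

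Much of this stands, and it limits what can be claimed. A reader might infer that nobody is blinded, that every inpatient knows the arm, or that controls are never checked. The documents support none of these: patient-facing labels and the look of the powder are not described, surgeon blinding at enrolment and coded samples remain, and checks in one arm only are one reading among several.

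The contradiction itself is not answered. More detail on masking would not turn a mealworm drink and confectionery without a control counterpart into matched items. Nor would it blind a dietitian who records them, or make a question about the mealworm neutral.

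**Conclusion.** The concern holds as a contradiction within the protocol article. Blinding of all parties, as stated in the title, Recruitment of study participants and Blinding, is not a property of the design described in Table 2 and Monitoring and follow-up period. At least the dietitian and the monitoring researcher cannot be blinded as described, and patient blinding in hospital is doubtful. For the researcher, this takes the wording of the checks at face value.

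No size can be put on the bias. A reader might infer that it favours mealworm, but the sign cannot be derived either: prompts in one arm could raise intake there, while knowing that one is eating insects could lower intake or the willingness to continue. PG-SGA, diary intake, adherence and withdrawal are the most exposed. The InBody primary outcome is exposed mainly through intake and any unequal adherence checks. The article does not say that the dietitian who surveys meals also takes the InBody reading, so direct measurement bias should not be assumed.

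**What to change.** 1. Restate in the title, Recruitment of study participants and Blinding who is blinded, to what and until when. Drop the double-blind label unless matched masking of both the meals and the powder is in place and can be described.
2. Reword the 1-week and two-weekly checks to refer to the study powder, and carry them out identically in both arms.
3. Have InBody and PG-SGA done by existing nutrition-team members who do not handle that patient's meals or diary. Keep the coding of blood samples as planned.
4. Interpret PG-SGA and intake as potentially unblinded outcomes, and say so in the conclusions.

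The cost is a change of wording and a small change to the nutrition team's rota. The trial may lose the double-blind label. Items 2 and 3 help only patients not yet followed up; items 1 and 4 can be done at any stage.

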#### Data management

The amount of food consumed by the patient daily will be assessed as a diary entry. The researcher collects the bags left over from the patients at the outpatient clinic. Individual participant medical information obtained as a result of this study is considered confidential and disclosure to third parties is prohibited. Blood samples transferred to the laboratory of Gangnam Severance Hospital will be identifiable by unique trial numbers only. Results related to nutrient indicators (Inbody, PG-SGA) will be managed by a Gangnam Severance Nutrition Team. The blood sample associated with the immune function test will be transferred to the lab of the study staff in Gangnam Severance Hospital, which will then undergo FACS (Fluorescence-activated cell sorting).

#### Withdrawal and reporting of adverse effects

If patients wish to voluntarily withdraw from the study, the patient will be asked if they would be given medical care until any AE symptoms resolve or the patient’s condition becomes stable.

Patients can quit the trial at any point without the need to give reasons for their decisions. If voluntary withdrawal occurs prior to diet intervention, the patient will not be randomized, and no more trial data will be collected for that patient. Patients can also withdraw from the trial following diet intervention.

#### Statistical methodology

All data will be entered into a single Microsoft Excel spreadsheet with participants identified only by their unique subject number. All entries will be double-checked by another member of the research team. Statistical analysis will be performed using IBM SPSS version 21.0 (IBM Corp; released 2012. IBM SPSS Statistics for Windows Version 21.0. Armonk, NY, USA). The mean difference in nutrient intakes, changes in body measurements, changes in body composition, and PG-SGA scores will be calculated using the Wilcoxon signed rank test and the Mann Whitney test.

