### Sample size calculation

The output of the sample size will be based on an independent two-sample t test. It is expected that there will be a difference in body cell mass between the standard meal group (control) and the group ingesting the mealworms. Assuming an alpha value of 0.05 and 1-β (power) of 0.8, 75 samples will need to be obtained for each group; considering the dropout rate of 10%, 84 samples will need to be obtained for each group. The total of the two groups is 168. The primary endpoint will be the number of subjects and body cell mass. A comparison will then be made between the two groups at 2 months. A subgroup analysis of pancreatobiliary and liver disease will also be performed as a secondary endpoint. Patients with pancreatobiliary and liver disease in our clinic have a 2:1 ratio. Therefore, the 168 patients were divided into two groups: one with 112 patients and the other with 56 patients. Patients with pancreaticobiliary disease (Group A & B) and liver (Group C) disease were assigned through stratified randomization. Pancreatobiliary disease group is divided into enteral feeding group(Group A) and non enteral feeding group.(Group B).

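### The stated rank tests do not give the promised mean difference, do not match the t test behind the sample size, and make only partial use of baseline and none of the randomisation stratum

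*Protocol article*

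**What the plan says.** - **Analysis.** The Statistical methodology section has one sentence on methods. It covers nutrient intakes, changes in body measurements, changes in body composition, and PG-SGA, refers to their mean difference, and ends "PG-SGA scores will be calculated using the Wilcoxon signed rank test and the Mann Whitney test". It names no other test or model.
- **Endpoint.** Study objectives and endpoints sets the primary endpoint as body cell mass index 2 months after surgery. Outcome measures says it comes from the body-composition device, so it belongs to one of the categories in the analysis sentence.
- **Sample size.** "The output of the sample size will be based on an independent two-sample t test". The section then says "Assuming an alpha value of 0.05 and 1-β (power) of 0.8, 75 samples will need to be obtained for each group", gives no difference or SD ("It is expected that there will be a difference in body cell mass"), and plans the comparison of the two groups at 2 months.
- **Randomisation.** Allocation is 1:1 (Randomization). Sample size calculation says that patients with pancreatobiliary (Groups A and B) and liver (Group C) "disease were assigned through stratified randomization".
- **Baseline.** Table 4 lists body composition and PG-SGA among the assessments and appears to mark them at Day -1 and day 60. Its layout is broken in the text at hand.

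**The concern.** Four things do not fit together.

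1. The sentence promises mean differences, but the two named tests give p-values. As written, the primary question has no stated effect estimate to go with its test.
2. The signed rank test is paired. In a two-arm parallel trial it can test only before against after, within an arm or pooled, so it cannot answer the randomised question. The sentence lists it alongside Mann-Whitney without saying what each is for.
3. The trial is sized for a t test comparing the arms at 2 months, yet the analysis names rank tests on changes. Both the test and the scale differ.
4. Baseline enters only by subtraction, and the factor used to stratify randomisation does not enter the stated tests. A model using both would need no data beyond what the trial appears to collect.

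At stake are an interpretable estimate for the primary endpoint and some precision. The validity of the between-arm comparison is not in question.

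**Working it through.** **Reproducing the plan's figures.** 75 / 0.9 = 83.3, rounded up to 84 per arm; 2 x 84 = 168. Both agree with the protocol. The 75 itself cannot be reproduced, because no difference or SD is given.

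**Implied effect.** Assume two-sided alpha 0.05 (sidedness is not stated) and 80% power:

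d = (1.960 + 0.842) x sqrt(2/75) = 2.802 x 0.1633 = 0.457

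The exact t version gives 0.460. A one-sided test would imply 0.406. The steps below use the two-sided normal approximation, with d about 0.46.

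**Cost of the rank test alone.** Under normality Mann-Whitney has relative efficiency 3/pi = 0.955. Power = Phi(2.802 x sqrt(0.955) - 1.960) = Phi(0.778) = 78.2%, against 80% for the t test. Holding 80% would take 75 x pi/3 = 78.5, that is 79 per arm before dropout.

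**Value of baseline adjustment, d on the 2-month value.** Let r be the correlation between baseline and 2-month values (not in the document, so assumed), with equal SDs at both times. The SD of change is multiplied by sqrt(2(1 - r)) and the ANCOVA residual SD by sqrt(1 - r^2).

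- Mann-Whitney on change: power = Phi(2.802 x sqrt(0.955) / sqrt(2(1 - r)) - 1.960)
- ANCOVA: power = Phi(2.802 / sqrt(1 - r^2) - 1.960)

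| r | Mann-Whitney on change | ANCOVA | Gain (points) |
|---|---|---|---|
| 0.3 | 63.8% | 83.6% | 19.8 |
| 0.5 | 78.2% | 89.9% | 11.7 |
| 0.7 | 94.2% | 97.5% | 3.3 |
| 0.8 | 99.1% | 99.7% | 0.6 |

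A simulation with 4,000 runs per setting and d = 0.460 agrees: 77.8% against 89.7% at r = 0.5, and 94.4% against 97.4% at r = 0.7.

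**The same, d on change.** Mann-Whitney on change then stays at 78.2% whatever r is. The ANCOVA residual SD relative to the SD of change is sqrt((1 + r)/2), so power = Phi(2.802 / sqrt((1 + r)/2) - 1.960).

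| r | Mann-Whitney on change | ANCOVA | Gain (points) |
|---|---|---|---|
| 0.5 | 78.2% | 89.9% | 11.7 |
| 0.7 | 78.2% | 86.0% | 7.8 |
| 0.9 | 78.2% | 82.0% | 3.8 |

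**Stratum.** The gain from adjusting for disease cannot be computed, because the document gives nothing on how body cell mass index differs between the strata.

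**The case against.** The strongest reply is that Mann-Whitney is a valid test of the randomised contrast, costs about 2 points under normality, and can match or beat the t test when data are far from normal. That stands. A reader might infer that the between-arm test is invalid, and the documents do not support it. For PG-SGA, a scored scale, a rank test is defensible.

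The reply also limits four other tempting readings.

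- **That baseline is ignored.** It is not: the sentence analyses changes. For the same reason, comparing ANCOVA with Mann-Whitney on raw 2-month values (78% against 97.5% at r = 0.7) overstates the loss. The fair comparator is Mann-Whitney on change, where the gain at r = 0.7 is about 3 points.
- **That within-arm p-values will decide efficacy.** With 50% power for change in each arm, exactly one arm would be significant 2 x 0.5 x 0.5 = 50% of the time even if the arms do not differ. But the protocol plans no such claim, and the sample size section makes the comparison between groups.
- **That the primary endpoint is certain to be tested only by ranks.** The sentence does not name body cell mass index, so a t test on the 2-month value is not excluded. The conflict is that the sizing section and the only analysis sentence, which covers the endpoint's category, point to different tests.
- **That the model should adjust for Groups A, B and C.** The stated stratum is pancreatobiliary versus liver. The A/B split follows the operation and feeding route and may be settled after randomisation, which takes place before surgery.

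Finally, covariates and confidence intervals are often left to a statistical analysis plan, and this is a condensed article. Their absence alone would be no finding. The point rests on what the article fixes: named tests, a quantity they do not produce, and a sample size built on another test. That Table 4 shows baseline body composition is an inference, but analysing changes requires such a measurement.

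**Conclusion.** The point holds at moderate severity, as a design-analysis mismatch and a missed gain in estimation and efficiency. That neither named test yields a mean difference, that the signed rank test does not compare the arms, and that the sizing test differs from the analysis tests all follow from the text without numerical assumptions.

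The power figures do rest on assumptions: two-sided alpha, normal data, equal SDs, 75 evaluable patients per arm, and assumed correlations. ANCOVA had the higher power at every correlation tabulated. The gain can be material at a correlation of 0.5 or below. With the effect on the 2-month scale it is negligible at 0.8 or above. With the effect on the change scale it is still about 4 points at 0.9.

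**What to change.** Replace the analysis sentence with a short paragraph:

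- **Primary endpoint.** Compare day-60 body cell mass index between arms by ANCOVA, with baseline body cell mass index and the randomisation stratum (pancreatobiliary versus liver) as covariates. Report the adjusted mean difference with its 95% CI.
- **Other continuous body-composition endpoints.** Use the same model, with each measure's own baseline.
- **Mann-Whitney.** Keep it as a sensitivity analysis; it may remain the test for PG-SGA.
- **Signed rank test.** Use it descriptively only, for change within an arm.

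The sample size can stay at 168. Under the assumptions above, ANCOVA has more power than the t test the trial was sized on when that effect is on the same scale. The cost is one paragraph of wording, settled before the data are analysed. It needs no new patients or visits and no measurements beyond those the trial appears to collect, and it runs in the software already named.
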